## ACRONYMS

|         |                                                |
|---------|------------------------------------------------|
| ACASI   | Audio Computer-Assisted Self-Interview         |
| ART     | Antiretroviral therapy                         |
| BBST    | Blood-based self-test                          |
| CeSHHAR | Centre for Sexual Health and HIV/AIDS Research |
| HIVST   | HIV self-testing                               |
| MRCZ    | Medical Research Council of Zimbabwe           |
| PSI     | Population Services International              |
| RDT     | Rapid diagnostic test                          |
| SMS     | Short Message Service                          |
| SRA     | Stringent Regulatory Authority                 |
| SSA     | Sub Saharan Africa                             |
| STAR    | Self-Testing in Africa                         |
| UNAIDS  | Joint United Nations Programme on HIV/AIDS     |
| WHO     | World Health Organization                      |

## BACKGROUND

Although there are over 25 million people living with HIV in Sub-Saharan Africa (SSA), about half of them are unaware of their status. Universal HIV testing uptake is therefore a critical first step towards ending the HIV/AIDS epidemic and represents the largest obstacle to meeting the first of the UNAIDS 90-90-90 targets – that is, by 2020, 90% of all people living with HIV should know their HIV status. Certain populations are disproportionately vulnerable and at elevated risks of HIV infection, including young women and adolescent girls as well as key populations such as sex workers and men who have sex with men. However, current HIV testing services approaches do not reach everyone, most often either because services are not accessible to them or because people are concerned about lack of privacy and fear of stigma and discrimination. Consequently, many people living with HIV only present at health care facilities late in their infection when they are already ill, reducing their chance of successful treatment.

**HIV self-testing is a promising approach to increase HIV testing uptake.** The WHO defines HIV self-testing (HIVST) as a specific process in which a person collects his or her specimen (oral fluid or blood), performs a test, and interprets the result, often in private. Self-tests can circumvent a number of structural and health systems barriers to uptake of HIV testing. With the development of simple, oral fluid-based tests that have achieved high sensitivity and specificity, a number of countries in SSA are developing policies to implement and support self-testing and the WHO has recently called for the scale-up of HIVST. Research conducted in a number of different countries, including Zimbabwe, shows high acceptability of and interest in self-testing across a wide range of populations as well as high accuracy in the hands of lay users. By having the potential to reach first-time testers and non-frequent testers, individuals with undiagnosed HIV, and those at ongoing risk who need frequent retesting, HIVST is a promising and innovative approach to increase HIV testing uptake. As countries consider alternative ways to scale-up HIVST, it is essential to know the demand for self-test kits in the general population and in high-risk segments of the population. In particular, knowing what the demand for self-tests might be at various prices is important for developing optimal pricing strategies – and subsidy levels – for the test kits. It is also vital to understand the implications of self-test pricing policies for the demand that can be expected by high-risk individuals who do not typically access other HIV testing modalities.

**Novel rapid diagnostic tests for HIV self-testing are available, but evidence on its effectiveness and implementation strategies in low-resource settings is lacking.** There are currently three HIVST products, one oral fluid-based and two blood-based rapid diagnostic tests (RDTs), that are approved by a Stringent Regulatory Authority (SRA), but all of these are in high income countries: Oraquick In-Home HIV Test (Orasure Technologies USA), an oral fluid RDT, is available in the United States; blood-based RDTs are available in France (Autotest VIH, AAZ Labs, France) and the United Kingdom (BioSure HIV Self-Test, Biosure Ltd., United Kingdom). Only one of the current RDTs for HIVST is WHO prequalified, which facilitates registration in resource-limited countries in SSA. In addition, at least six blood-based RDTs and three oral fluid-based RDTs for HIVST are currently under consideration or in development. The majority of these products are intended for low and middle-income markets, including SSA, with most manufacturers expecting demand in these target markets to be coming from the public sector (e.g. governments and international donors).

**Because HIV self-tests have the potential to be a game changer in increasing HIV testing uptake, there is considerable interest in what strategies are optimal for distributing self-tests and what prices (if any) should be charged for self-tests.** As countries consider alternative ways to scale-up HIVST, it is essential to know the demand for self-test kits in the general population and in high-risk segments of

the population. In particular, knowing what the demand for self-tests might be at various prices is important for developing optimal pricing strategies – and subsidy levels – for the test kits. It is also vital to understand the implications of self-test pricing policies for the demand that can be expected by high-risk individuals who do not typically access other HIV testing modalities. Generating real world evidence on the public health and subsidy implications of different pricing policies for self-tests can provide the information that donor organizations and country governments need for making important decisions.

**A field experiment can address the evidence gap and inform policy decisions regarding the optimal pricing policies and distribution strategies for HIV self-testing.** To fill the evidence gap and inform policy decisions, we propose to conduct a field experiment to obtain “revealed preference” estimates of the likelihood that individuals will purchase oral fluid-based and blood-based HIV self-tests at alternative prices. Such an approach is useful for estimating the price sensitivity (or elasticity) of demand for self-tests. Economists have conducted field experiments to determine the demand for various essential healthcare products in many countries including Kenya, Zambia, and Malawi. These products include antimalarial bed nets, medical male circumcision services, and chlorine-based water treatment products – the results of these studies have been informative in policy debates about whether it is preferable to charge for essential healthcare products (partial government subsidy) or offer them for free instead (full subsidy). The proposed field experiment for HIV self-tests will also estimate the extent to which demand for self-tests differs by certain distribution channels such as retail outlets, public sector health facilities, and other community-based venues. Importantly, the experiment will also test whether the provision of HIV self-tests can be targeted more cost-effectively to reach high-risk persons and non-recent testers by examining the demand for self-tests in these populations in responses to various prices and distribution strategies. Last, with additional funding in the future, we will explore whether demand for repeated HIV self-testing is contingent on the price offered initially. The results of the study will provide vital information required by policy makers and implementers on the optimal pricing and distribution strategies for introducing HIV self-tests and scaling up HIVST in resource limited settings.

## **SPECIFIC AIMS**

The specific aims of the proposed study are as follows:

- Aim 1: Estimate demand for oral fluid-based and blood-based HIV self-tests at different out-of-pocket prices and determine the sensitivity of demand to various distribution strategies.
- Aim 2: Determine whether there are differences in HIV testing history and HIV risk profile of individuals who purchase or obtain HIV self-tests at low vs. high prices.
- Aim 3: Examine whether individuals’ demand for repeat self-test purchases is contingent on initial prices (with additional funding in the future).

## **STUDY DESIGN**

### **Overview of Study Design**

We will conduct a rigorous field experiment in urban and rural communities near Harare, Zimbabwe, to estimate individuals’ demand for oral fluid-based and blood-based HIV self-tests. About 4,000 adults will be randomly selected in study communities, administered a short questionnaire, and given referral vouchers that will enable them to obtain HIV self-tests at randomly allocated prices and distribution sites. All participants will be given a brief description of HIVST during the time of enrollment. In addition, all self-tests will include easy-to-use instructions that have been carefully developed based on prior studies in Zimbabwe. A link to an instructional video may also be provided to those who have access to a

phone and express interest in receiving a link to the video. Uptake of HIVST will be monitored at the distribution sites, where the vouchers will be collected in exchange for self-tests; the voucher numbers will enable us to link HIVST uptake to individual participants.

In a subsequent study with additional funding, we will also seek to determine the long-term implications of offering self-tests at very low prices initially; specifically we will assess whether free distribution initially suppresses individuals' willingness to pay for self-tests in the future. Roughly 12 months after the initial voucher offer, participants who provided a mobile phone number they can access within their household will be contacted via phone-based text messages and offered the same HIV self-tests again at one common non-zero price. The purchases at 12 months will once again be monitored and linked to participants via a unique identifier that is included in the text messages.

In Aim 1, we will generate estimates of the price sensitivity of demand for self-tests and also determine how the demand varies by distribution channels. In Aim 2, we will perform sub-group analyses to test whether key segments of the population are different in their likelihood of purchasing self-tests at various prices and distribution channels. This will indicate whether HIV self-tests can be targeted more cost-effectively to priority groups, such as those who do not typically use facility-based testing services. In Aim 3, we will explore to what extent individuals' demand for repeated self-testing is contingent on the price that is initially offered to them. This is a relevant question to understand whether HIV self-tests can facilitate repeated testing among high-risk individuals and whether offering HIV self-tests for free or at low price initially has long-term implications for the prices that can be charged. Separately, we will explore whether promotion messages on the vouchers have an effect of HIVST uptake.

### **Study Locations**

The study will be conducted in collaboration between MoHCC, PSI/Zimbabwe and the Centre for Sexual Health and HIV/AIDS Research (CeSHHAR) Zimbabwe. The proposed study will take place in two locations: 1) Seke Rural, a rural district in Mashonaland East province, and 2) Bindura Urban, a high density area in Mashonaland Central.

### **Eligibility Criteria**

Individuals who meet with study staff will be screened for the following eligibility criteria:

- Age 16 years or older
- Willing and able to provide written informed consent for participation
- Intends to stay in the study area for at least 12 months

### **Consent and Enrollment Processes**

Households in the study locations will be randomly selected using a door-to-door strategy. In each household, research assistants will randomly select one eligible individual and invite them to participate in the study, following a standard randomization protocol. Research assistants will review the informed consent form with eligible individuals. Those who provide consent will be enrolled into the study and administered a brief baseline questionnaire.

### **Randomization Procedures**

After completing the baseline questionnaire, participants will be given general information about HIVST and then assigned to one of the experimental arms based on computer-generated randomization. Participants will be given one referral voucher that offers a self-test kit at the random price and distribution site determined on the tablet computer. The vouchers will be valid for one month after the enrollment date – meaning that individuals will have up to one month to decide whether to

purchase/obtain self-tests. Each voucher can be used to redeem one self-test kit at the specified price and distribution site. The other household members above 16 years of age will also be offered one voucher per person. Vouchers for the same household will have the same price, distributor, and promotion messages.

Research assistants will clearly explain to participants how they can redeem the voucher. The out-of-pocket price that participants must pay for self-tests will be written clearly on the voucher and will range from \$0 (free/fully subsidized) to up to \$3. Up to five different prices will be used in the study and all of the prices will be below the current full market value of self-tests, meaning that all participants will be offered self-tests at a discounted price. Each voucher will have a unique identifier to determine whether the participants obtained self-tests within one month at the distribution sites. Computer-generated block randomization will be used to determine the sequence of prices & distribution sites on vouchers.

Distribution channels at which the self-tests will be sold or offered will be determined in consultation with PSI/Z and CeSHHAR staff. In rural communities, the distribution channels may include community health workers and retail shops to ensure access for all participants. In urban areas, the distribution channels may include pharmacies and local clinics.

Roughly 12 months after the enrollment ends, participants who own a cell phone will be offered the same HIV self-tests at one common price through short message service (SMS). This offer will be made by text message containing a unique number, and participants will be told they can purchase up to two self-tests by showing the text message to the staff at various distribution sites within one month. A unique identifier will be included in each text message and recorded at the time of sale in order to determine which participants purchased self-tests.

### **Data Collection Activities**

*Baseline data.* At the time of enrollment, participants will be administered a baseline questionnaire to record information on demographic characteristics, contact information, prior HIV testing history, and self-reported sexual behavior. Data will be recorded on encrypted, password-protected tablet computers. Participants will then be assigned to one of the experimental arms based on computer-generated randomization that is performed on the tablet computers. The result of the randomization will be recorded by research assistants, including the price, distribution site, and the unique identifier on each voucher.

*Demand for HIV self-tests.* To purchase oral fluid-based or blood-based HIV self-tests at subsidized prices with the paper voucher, participants must present the voucher in person within a month at the designated distribution site and pay the price specified on the voucher. The distribution sites will collect the vouchers, dispense HIV self-tests at the specified prices, and record the date of the transaction on the voucher.

*Demand for repeat testing.* To purchase HIV self-tests during the repeat testing portion of the study, participants must show the text message to the staff at designated distribution sites and pay the common price that will be established. Using a pre-distributed list of all cellphone numbers that were included in the study or an electronic system where cell phone numbers can be entered and confirmed, the distribution sites will verify that the participant is eligible to purchase self-tests and then dispense self-tests at the common price. The unique number included in the text message will be recorded so that it is possible to determine which participants purchased self-tests.

Study staff will undergo comprehensive training on the study design and methods, and we will also work closely throughout the study with the distribution sites to make sure they understand the purpose of the study and can perform relevant tasks. We will conduct weekly phone calls with designated staff at each distribution site to answer questions and resolve issues. Research assistants will collect the paper vouchers from the distribution sites approximately one month after enrollment ends and similarly will collect the redemption records one month after the text-message offer.

### **Outcomes**

The primary outcome will be the proportion of individuals that purchased or obtained at least one HIV self-test in each of the study groups. This will enable us to estimate the proportion of individuals who would buy self-tests at various prices, and the proportion of individuals who would buy self-tests at various combinations of price and distribution site.

In addition, we will examine how the likelihood of purchase vary by price and distribution site in key segments of the population, including individuals who have and have not tested for HIV in the past, individuals with low and high risk of HIV infection based on self-reported sexual behavior, and individuals with low and high income.

Finally, with additional funding in the future, we will compare the proportions of individuals who purchase HIV self-tests at the common price offered at about 12 months based on whether they initially received a partially or fully subsidized price. This will enable us to explore whether individuals' demand for HIV self-tests over the long term is contingent on the price that is initially offered to them.

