### **Statistical Analyses**

We will perform chi-squared tests to compare uptake at various non-zero prices to uptake at the price of zero (i.e. free distribution). We will also use regression analyses to estimate the elasticity (i.e. price-sensitivity) of the demand for self-tests. We will estimate unadjusted regression models as well as adjusted regression modes that include covariates such as individual characteristics, particularly those that differ between study groups. The subgroup analyses will be performed by comparison of means and by regression analyses that use interaction terms. Robust standard errors that allow for clustering of standard errors within communities and households will be reported for all regressions.

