### **Sample Size and Power Calculation**

The power analysis for this study focused on the primary outcome that compares the proportion of individuals who purchased at least one HIV self-test with vouchers at low vs. high price points. The power calculations allow for analyses to be stratified by rural vs. urban clusters. Assuming 15% of individuals would make a purchase when offered the highest price, the sample size required to detect a 10-percentage-point increase in the percentage of individuals who purchase at lower prices will be 270 per group (80% power and a type I error of 0.05). Thus, a sample size of about 2,000 adults in rural areas and 2,000 adults in urban areas (for a total sample of about 4,000 adults) will allow for five different price points to be used in each area.

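### Income and HIV risk are set up as low/high segments with no cut point; testing their interaction with price as two groups would waste information that the collected measures could keep

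*Protocol*

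**What the plan says.** The Outcomes section says that purchase will be examined by price and distribution site in key segments. Besides people who have and have not tested before, these are "individuals with low and high risk of HIV infection based on self-reported sexual behavior, and individuals with low and high income". No cut point, score or scale is given for either measure.

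The Overview of Study Design says that Aim 2 uses subgroup analyses to test whether such segments differ in their likelihood of purchase across prices and channels. The Statistical Analyses section gives the method: "The subgroup analyses will be performed by comparison of means and by regression analyses that use interaction terms". It does not say whether the modifier enters as two groups, a score or a continuous term.

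Under Data Collection Activities, the baseline questionnaire is to "record information on demographic characteristics, contact information, prior HIV testing history, and self-reported sexual behavior". Income is not named separately.

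The Sample Size and Power Calculation section covers only the primary price comparison. No power is stated for any segment interaction.

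**The concern.** Income is a graded quantity. Risk built from several reported behaviours is at least ordered. Splitting either into low and high treats people just either side of the cut as opposites, and people far apart on the same side as alike. If the segments are tested in that form, the interaction with price is estimated with less information than the questionnaire supplied, and the answer also depends on a cut not yet chosen.

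The Background gives weight to whether self-tests can be targeted to high-risk people, and risk profile is part of Aim 2. A real gradient in price response could be missed and then read as price making no difference to who obtains a test. The avoidable loss falls on secondary tests that have no stated power.

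**Working it through.** **1. The plan's own figure.** Inputs from the Sample Size and Power Calculation section: "Assuming 15% of individuals would make a purchase when offered the highest price"; a sample to "detect a 10-percentage-point increase in the percentage of individuals who purchase at lower prices"; 80% power; type I error 0.05, taken as two-sided.

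- Without continuity correction: n = [1.96·√(2·0.20·0.80) + 0.842·√(0.15·0.85 + 0.25·0.75)]² / 0.10² = 250.
- With continuity correction: (250/4)·[1 + √(1 + 4/(250·0.10))]² = 62.5·(1 + √1.16)² = 269.6, so 270.

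The stated 270 per group reproduces. It concerns price groups only, and the segment question does not touch it. With "2,000 adults in rural areas and 2,000 adults in urban areas" and five prices, there are about 2,000/5 = 400 per price per area.

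**2. Information kept by a split.** The documents give no distribution for income or risk, so those below are assumptions. Price is randomised, hence independent of the modifier. For a linear interaction, the share of information kept is then r = corr(x, d)², where x is the measure and d its two-group version. For a normal x cut at quantile p, r = φ(z_p)²/[p(1 − p)]. A test with 80% power on the full scale then has power Φ(√r·(1.96 + 0.842) − 1.96).

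| Assumed measure and cut | Kept | Lost | Power, from 80% |
|---|---|---|---|
| Normal, median | 0.637 (= 2/π) | 36% | 61% |
| Normal, 1/3–2/3 | 0.595 | about 40% | 58% |
| Normal, 80/20 | 0.490 | 51% | 50% |
| Uniform, median | 0.75 | 25% | 68% |
| Four equal levels, middle cut | 0.80 | 20% | 71% |
| Three levels (50/30/20%), lower cut | 0.803 | 20% | 71% |
| Three levels (50/30/20%), upper cut | 0.693 | 31% | 64% |
| Lognormal raw income, σ = 0.5, median | 0.517 | 48% | 52% |
| Lognormal raw income, σ = 1, median | 0.27 | 73% | 31% |
| Yes/no risk item | 1.00 | 0% | 80% |

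Worked example, four equal levels scored 0–3 and cut in the middle: covariance = (2 + 3)/4 − 1.5·0.5 = 0.5, and the variances are 1.25 and 0.25, so r = 0.5²/(1.25·0.25) = 0.80. An outer cut of the same score keeps only 0.60. An uneven four-level score (60/25/10/5%) keeps 0.73, 0.72 or 0.41, depending on the cut.

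**3. Simulation checks.** All used 4,000 people, five prices from $0 to $3, and a linear probability model with robust standard errors.

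- Normal measure, linear gradient: power 80% on the full scale, 60% after a median split.
- Uniform measure, linear gradient: 80% against 66%.
- True effect a step at the cut: 44% on the continuous term, 60% with the split.
- A separate run with a continuous measure, a five-level score and a median split: 78.6%, 72.9% and 58.5%. Type I error was about 5% for all three.

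**4. Against a realistic alternative.** In practice the alternative is banded income or an ordered score, so the five-level score is the fair comparator. Moving from 72.9% to 58.5% power implies kept information of [(0.215 + 1.96)/(0.610 + 1.96)]² = (2.175/2.570)² = 0.72, a loss of 28%.

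**The case against.** - **The protocol does not literally say that the measures are cut before the interaction is tested.** This is correct: the form of the modifier is left open, and coding is often left to an analysis plan, which is not shown here. What remains is that the protocol itself describes two-group segments, says that segments are tested, and offers no graded alternative. An analysis plan that followed it would inherit the loss.
- **A reader might infer that a third or more of the information is always lost.** The documents do not support that, since they give neither the distribution nor the shape of the gradient. The loss is below a third for a uniform measure and for most short scores tried, and is nil for a yes/no item. If the true effect is a step at the cut, the split has more power.
- **A reader might infer that income is not collected.** That does not follow. The baseline list ("demographic characteristics, contact information, prior HIV testing history, and self-reported sexual behavior") gives categories, not items, and the demographic category may include income. Nor would an uncollected variable explain an information loss; it could not be analysed at all.
- **Group contrasts are legitimate and easy for policy makers to read.** This stands, and is a reason to keep low/high groups for presentation.
- **The stakes are limited.** Also fair. These are secondary analyses, income is not named in Aim 2, the tested/not-tested segment is unaffected, and the part of Aim 2 that compares purchasers at low and high prices could use a graded risk measure without any split.

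**Conclusion.** The point holds as a conditional inefficiency in secondary analyses. On the natural reading of the Outcomes, Overview and Statistical Analyses sections, graded income and risk measures are tested as two groups with undefined cuts. With a roughly normal measure and a linear gradient, a median split costs about 36% of the information, as if about 0.637 × 4,000 = 2,550 of the 4,000 participants had been analysed. For ordered scores of three to five levels, about 20–31% is a fair range, with more lost at extreme cuts. The 80% starting power is illustrative, because the protocol states none for these tests. Nothing here bears on the primary outcome, the type I error of the tests or the sample size.

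**What to change.** In the Outcomes and Statistical Analyses sections, state that the price-by-income and price-by-risk interactions are tested on the measure as collected:

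- Income: bands or an asset score, entered as an ordered score. If a log transform is used, say how zero incomes are handled.
- Risk: a prespecified count or ordered score of reported behaviours.
- Linearity: check by refitting with the banded version, which would also show a step.
- Low/high groups: keep them for descriptive tables and policy presentation, with the cuts fixed in advance.

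Naming income in the baseline list under Data Collection Activities would be a helpful clarification only.

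The cost is a wording change. The small downside is the linearity assumption in the main interaction test. No change to the sample size is needed.

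### Aim 3 asks how later demand depends on the initial price, low prices included, but the stated 12-month comparison is only free versus all paid prices together

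*Protocol*

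**What the plan says.** Four places in the Protocol bear on Aim 3.

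- **Specific Aims.** The question is whether repeat demand "is contingent on initial prices". The plural is general and covers the whole price range.
- **Overview of Study Design, description of the aims.** The policy question is "whether offering HIV self-tests for free or at low price initially has long-term implications for the prices that can be charged". Low prices are named beside free.
- **Overview of Study Design, description of the subsequent study.** The purpose is to "determine the long-term implications of offering self-tests at very low prices initially", but the same sentence then narrows: "specifically we will assess whether free distribution initially suppresses individuals' willingness to pay for self-tests in the future".
- **Outcomes.** Purchase at the common 12-month price will be compared "based on whether they initially received a partially or fully subsidized price". The next sentence says that this will let the investigators explore whether "demand for HIV self-tests over the long term is contingent on the price that is initially offered to them".

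Randomization Procedures settles what the two groups are. Prices run from $0, glossed there as fully subsidized, to at most $3. "Up to five different prices will be used in the study", and all lie below market value. Every non-zero price is therefore a partial subsidy, and the comparison in Outcomes is $0 against every paid price.

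**The concern.** The comparison in Outcomes and the inference drawn from it in the next sentence do not match. A two-group contrast yields one number, the difference between free and the average of the paid arms. It cannot show whether later demand rises or falls across initial prices. It also gives no estimate for the low-price arms, because these sit in the comparison group with the highest prices.

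What is at stake is how the result would be read. Suppose low initial prices lower later demand about as much as free provision does, which the Overview of Study Design treats as an open question. The free-versus-paid difference would then be smaller than free versus high price, and a small difference could be reported as little dependence on initial price. A programme deciding whether to launch at a low price would have no result for that choice, although the trial randomised people to it.

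**Working it through.** **The plan's own figure.** Sample Size and Power Calculation gives 270 per group for 15% versus 25%, 80% power and type I error 0.05. This is for the initial voucher; no figure is given for the 12-month comparison. Taking the test as two-sided:

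- Uncorrected: n = [1.96 × √(2 × 0.20 × 0.80) + 0.842 × √(0.15 × 0.85 + 0.25 × 0.75)]² / 0.10² = 250.
- With continuity correction: n = (250/4) × [1 + √(1 + 4/(250 × 0.10))]² = 270.

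The stated figure reproduces, and 5 × 270 = 1,350 fits within 2,000 per area. There is no arithmetic error in the plan.

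**What free versus paid estimates.** Inputs from the Protocol: up to five prices (free plus up to four paid) and about 4,000 participants. Assumed: five prices in equal arms, and a 12-month purchase rate of 15% where demand is suppressed and 25% where it is not. These rates borrow the figures of the plan's power calculation; the Protocol gives none for 12 months.

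If k of the four paid arms behave like free, and D is the difference between free and the unsuppressed arms, then

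free-versus-paid difference = D × (4 − k)/4.

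With D = 10 points:

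- k = 0: 10 × 4/4 = 10 points
- k = 1: 10 × 3/4 = 7.5 points
- k = 2: 10 × 2/4 = 5.0 points
- k = 3: 10 × 1/4 = 2.5 points

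For a straight gradient (15, 17.5, 20, 22.5, 25%), the paid mean is 85/4 = 21.25%, so the difference is 6.25 points against 10 for free versus the highest price.

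**Power.** Not everyone can be reached by phone at 12 months, and the share is not given. I take 100% (800 per price) and 50% (400 per price), with no allowance for clustering. The test for free versus paid compares n with 4n people. For k = 2 at n = 400, the overall rate is (0.15 × 400 + 0.20 × 1,600)/2,000 = 0.19. The null standard error is √[0.19 × 0.81 × (1/400 + 1/1,600)] = 0.0219. The alternative standard error is √(0.1275/400 + 0.16/1,600) = 0.0205. Then z = (0.05 − 1.96 × 0.0219)/0.0205 = 0.34, which is 63% power. The trend test uses five equally spaced scores.

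| Pattern | Difference, free v paid | Free v paid, 800 / 400 per price | Free v highest, 400 | Linear trend, 400 |
|---|---|---|---|---|
| Free only suppressed | 10 | >99% / >99% | 94% | 86% |
| Free + 1 low price | 7.5 | 99.9% / 93% | 94% | >99% |
| Free + 2 low prices | 5.0 | 91% / 63% | 94% | >99% |
| Free + 3 low prices | 2.5 | 39% / 21% | 94% | 91% |
| Straight gradient | 6.25 | 98.5% / 82% | 94% | 98% |

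The first row matters as much as the others: when carry-over is confined to the free arm, free versus paid is the stronger test.

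**The case against.** The best defence is the second half of the sentence in the Overview of Study Design, which says specifically that the question is whether free distribution suppresses later willingness to pay. The comparison in Outcomes answers exactly that. This stands, and it is why free versus paid should be kept. It does not cover the broader wording in Specific Aims, in the description of Aim 3, or in the concluding sentence of Outcomes.

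A second defence is that Statistical Analyses already plans price-by-price chi-squared tests and regressions, and is not labelled by aim. That section is worded for uptake at different offered prices, with an elasticity. At 12 months there is one common price, so the wording fits the initial voucher and not an analysis by initial price. It does suggest that working price by price is the investigators' habit. Each assigned price is recorded and linked to the 12-month sale, so by-price results remain obtainable. It would be too strong to infer that the study cannot answer the question.

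Third, detail of this kind may be left to a statistical analysis plan or to the later study's own protocol. That would answer a complaint about missing detail. Here the Protocol states a comparison and attaches to it a conclusion that the comparison does not support.

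Three stronger readings should be resisted:

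- A reader might call the free-versus-paid estimate biased towards zero. It is not: it is a valid randomised contrast for its own estimand, which differs from free versus high price.
- A reader might expect a null result. An exact zero needs a non-monotone pattern, for example free 20%, two low prices 15% and two high prices 25%, where the paid mean is 80/4 = 20%. That runs against the stated hypothesis that free provision suppresses demand.
- A reader might argue that carry-over reverses between arms that started below and above the common price. Nothing in the Protocol says so. The common price is not yet set, so such a contrast cannot be defined.

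**Conclusion.** The mismatch holds. The single 12-month comparison stated is suited to free versus paid, and does not support a conclusion, positive or negative, about dependence on the initial price in general or on low prices in particular.

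The size is conditional. If carry-over is confined to the free arm, nothing is lost. If one, two or three of four equal paid arms act like free, the contrast keeps three quarters, a half or a quarter of the free-versus-high difference. The quarter-per-arm rule needs only equal arms and equal suppression. The percentages and powers rest on assumed 12-month rates, an assumed phone share, equally spaced scores and no clustering. Reading the two groups as free and all paid prices together is the plain sense of the text, though the Protocol does not use the word pooled.

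Severity is low to moderate. Aim 3 is exploratory, depends on future funding and belongs to a subsequent study; the primary outcome and its sample size are unaffected.

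**What to change.** In Outcomes, replace the two-group sentence with a comparison of 12-month purchase at the common price by each randomised initial price. Add a test across initial prices, either overall or for trend, and keep free versus paid as a named contrast. Say which of these carries the Aim 3 conclusion. Alternatively, if free versus paid is all that is wanted, narrow Specific Aims, both descriptions in the Overview of Study Design and the closing sentence of Outcomes to that question.

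Either route changes wording only. The initial price is already randomised, recorded and linkable to the 12-month sale, so no new data or participants are needed. The statistical cost is that single-price contrasts are less precise. With equal arms and similar variances, the standard error of free versus one price exceeds that of free versus four prices together by a factor of √[(1 + 1)/(1 + 1/4)] = √1.6 = 1.26. Keeping the free-versus-paid contrast alongside preserves its precision for the narrower question.
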